### Recruitment, randomization, and blinding

2.5.

The Ultra-ECMO trial will include patients who meet the abovementioned eligibility criteria. Formal information about the trial and an official copy of the informed consent form will be sent to their guardians. We will assign participants to an intervention arm or a control arm in a random manner, with those in the former group receiving ultra-protective VT and those in the latter receiving 72 h of protective VT. Guardians will also be informed that they are allowed to drop out of the trial at any time.

The randomization list will be computer-generated according to a simple randomization principle using a ratio of 1:1 by the Clinical Research Board of the School of Public Health of Nanjing Medical University. Participants will be assigned to each group by an independent trial assistant after verification of patient eligibility. Once group allocation has been completed, local investigators will register the record, then reveal the group allocation to care providers, who will deliver the intervention.

Trial assistants responsible for group allocation will be blinded to both groups of patients, but blinding of care providers is impracticable as ventilatory settings and respiratory mechanics measurements are part of routine daily clinical practice. The outcome assessors, data analysts and statisticians will not know the group allocation.

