### Data collection and management

2.7.

The total duration of ECMO treatment, total time (in days) on IMV, ICU length of stay, analgesic/sedation dosage, all-cause hospital mortality, levels of inflammatory factors in BALF, LUS, amounts of fluid infusion, and total hospitalization cost will be calculated using patient medical records (Table 6).

**Table 6 T6:** Scheduled events and timeline for the ultra-ECMO trial.

		Study period					
Timepoint		Eligibility/Allocation	Post-Allocation			Close-out	
		T0 ECMO initiation	T1 24 h after ECMO	T2 48 h after ECMO	T3 72 h after ECMO	T4 28 days after ECMO	Tx ICU discharge day
Enrollment	Eligibility check	×					
	Informal consent	×					
	Allocation	×					
Intervention	Ultra-protective or protective VT group	×					
Assessments	Demorgraphic data	×					
	Comorbidity	×					
	Clinical characteristics	×					
	Respiratory mechanics parameters	×	×	×	×		
	LUS	×	×	×	×		
	Levels of inflammatory factors in BALF	×	×	×	×		
	In-hospital mortality		×	×	×	×	×
	RASS score	↔					
	VIS	↔					
	Amounts of resuscitative fluids		×	×	×	×	×
	Sedation and NMBA dose	↔					
	ICU LOS	↔					
	Total length of ECMO weaning	↔					
	Total lenght of IMV weaning	↔					
	Total cost for hospitalization						×
	Total hospital LOS	↔					
	28-day VFD	↔					

VT, tidal volume; VFD, ventilator-free day; ICU, intensive care unit; LOS, length of stay, VIS, vasoactive inotrope score; RASS, richmond agitation sedation scal; LUS, lung ultrasound score; BALF, broncho-alveolar lavage fluid.

We will not consider missing values for primary and secondary outcomes during hospitalization. However, missing values could appear specific to patients who survive to hospital discharge. If so, we will contact patients or their next of kin at day 28 to assess the pre-defined outcomes.

Clinical data will include but are not limited to general characteristics (age, sex, weight, height), comorbidities, original disease, the Acute Physiology and Chronic Health Evaluation II score, partial pressure of arterial oxygen/inspired oxygen fraction, PEEP, VT (in ml/kg of PBW), respiratory rate (in breaths/min), DP, P_plat_, P_es_, P_tp_, P_mean_ (in cm of water), C_stat_ (in ml/cmH_2_O), R (in cmH_2_O/L/s), arterial blood PaO_2_ and PaCO_2_ values (in mmHg), and mechanical power (in J/min).

We will also monitor the clinical conditions as well as the ECMO running status and collect any records.

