### Sample size calculation

2.8.

PASS 11 was used for sample size calculation, where a sample size of 292 patients per group would achieve 80% power to detect a difference between the two groups, providing the means were 7.1 and 9.2 with group standard deviations of 8.8 and 9.3 and with a significance level α of 0.05 using a two-sided two-sample *t*-test. Accounting for an anticipated dropout rate of 5%, 614 patients were required for the study.

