#### Primary outcome analysis

2.9.2.

The primary outcome is the 28-day VFD number, which will be determined by the intention-to-treat analysis (ITT) (21), regardless of whether the allocated ventilation strategy was effectively applied or not. The primary outcome will be reported in each group in the form of means with standard deviation values or medians with interquartile ranges. Student's *t* test or the Mann–Whitney *U* test will support related comparisons of the 2 groups while considering their distribution characteristics.

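### The rule that sets aside in-hospital missing values does not fit withdrawal at any time, the 5% dropout allowance, deaths tracked at T1–T3 and the intention-to-treat label

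*Protocol article*

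**What the plan says.** Section 2.7 takes most outcomes from the medical records and then states: "We will not consider missing values for primary and secondary outcomes during hospitalization". It continues: "However, missing values could appear specific to patients who survive to hospital discharge". For those patients there is a remedy: "If so, we will contact patients or their next of kin at day 28 to assess the pre-defined outcomes".

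Four other places bear on the same point:

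- Section 2.5: "Guardians will also be informed that they are allowed to drop out of the trial at any time".
- Section 2.8: "Accounting for an anticipated dropout rate of 5%, 614 patients were required for the study".
- Table 6 lists in-hospital mortality at T1, T2 and T3 (24, 48 and 72 h). Respiratory mechanics, lung ultrasound score (LUS) and inflammatory factors in lavage fluid (BALF) are due at the same times.
- Section 2.9.2 analyses the primary outcome, 28-day ventilator-free days (VFD), by intention to treat (ITT), "regardless of whether the allocated ventilation strategy was effectively applied or not". Section 2.9.3 applies ITT to the secondary outcomes and compares quantitative ones with a two-sample t or Mann–Whitney test.

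**The concern.** The sentence in Section 2.7 is a stated rule, so this is not a matter of detail left to an analysis plan. It can be read in two ways, and neither sits well with the other sections.

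- **Missing values are ignored.** Patients without an outcome then drop out of the test, which undercuts the ITT label.
- **Missing values are not expected.** This conflicts with withdrawal at any time, which includes the hospital stay, and with a sample size that allows for 5% dropout. For BALF, LUS and mechanics it also conflicts with the plan's own expectation that some patients may die by T1–T3. A patient who has died has no later measurement, and no record can supply one.

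ITT in Section 2.9.2 is defined by adherence to the ventilation strategy. It does not say how the VFD of a withdrawn patient is obtained. Care providers know the allocation, so withdrawal could depend on arm and prognosis. The sentence as written would permit a completer analysis of VFD to be reported as ITT. It would also permit T1–T3 tests in survivors only, which are biased if early mortality differs by arm.

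**Working it through.** **Inputs.** From Section 2.8: means 7.1 and 9.2 (difference 2.1 VFD), SDs 8.8 and 9.3, 292 per group, 80% power, two-sided α of 0.05, 5% dropout, 614 in total. Assumptions of this check: 9.2 (SD 9.3) is the intervention arm, VFD runs from 0 to 28, and 307 patients are randomised per arm.

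**1. The plan's own figure.** Pooled SD = √[(8.8² + 9.3²)/2] = √81.965 = 9.053. Then n = 2 × (1.960 + 0.842)² × 81.965 / 2.1² ≈ 292 per group, as stated. For dropout, 584 × 1.05 = 613.2, giving 614; 584/0.95 = 614.7 would give 615. The stated 614 is reproduced closely enough. The allowance is 614 − 584 = 30 patients, or 15 per arm (15/307 = 4.9%).

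**2. Precision among completers.** SE = √(8.8²/292 + 9.3²/292) = 0.749. The smallest significant difference is about 1.47 VFD. An observed 2.1 gives p = 0.005.

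**3. Filling in the missing patients.** With 15 missing per arm set to x_I (intervention) and x_C (control), the difference over all 614 is

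D = [292 × d + 15 × (x_I − x_C)] / 307,

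where d is the difference among completers. The pooled t-test is repeated with the SDs updated for the filled-in values. For d = 2.1, 292 × 2.1 = 613.2:

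| Missing intervention / control | D | p |
|---|---|---|
| 0 / 0 | 613.2/307 = 2.00 | 0.006 |
| 7.1 / 7.1 | 2.00 | 0.005 |
| 0 / 7.1 | (613.2 − 106.5)/307 = 1.65 | 0.023 |
| 0 / 11.8 | (613.2 − 177)/307 = 1.42 | 0.050 (tipping point) |
| 0 / 28 | (613.2 − 420)/307 = 0.63 | 0.41 |

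**4. Uneven dropout, all 30 missing at 0 VFD, d = 2.1.**

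| Missing intervention / control (number) | D | p |
|---|---|---|
| 20 / 10 | 1.73 | 0.018 |
| 25 / 5 | 1.47 | 0.044 |
| 30 / 0 | 1.20 | 0.10 |

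**5. Smaller observed effects, 15 missing per arm, missing intervention patients at 0.**

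| d among completers | Completer p | Control value that tips p to 0.05 |
|---|---|---|
| 2.1 | 0.005 | about 11.8 |
| 1.8 | 0.017 | about 6.1 |
| 1.6 | 0.033 | about 2.1 |
| 1.5 | 0.046 | about 0.1 |

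At d = 1.8 the tipping value is already below the assumed control mean of 7.1.

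**6. T1–T3 measures.** No arithmetic is possible, because the article gives no early mortality rate. Set side by side, Table 6 schedules mortality and the BALF, LUS and mechanics measurements at the same three times, and Section 2.7 sets aside missing values for those outcomes. The two-sample tests of Section 2.9.3 would then use only patients alive and measured.

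**The case against.** The strongest reply is about context. The contrast that opens the next sentence in Section 2.7 suggests the authors mean that in-hospital gaps are not expected, since outcomes come from the records. Where they do expect gaps, after discharge, they plan day-28 contact. Section 2.6 keeps patients with intervention-related adverse events in their allocated group. A reader might infer that the primary analysis will be a completer analysis. The article does not say so anywhere: Section 2.8 only enlarges the sample and does not define an analysis set. That part of the reply stands. It does not cover a patient withdrawn in hospital, because day-28 contact is for patients who survive to discharge and the retention rule in Section 2.6 concerns adverse events.

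A second reply is that Section 2.4 lists ventilation and ECMO of more than 72 h among the inclusion criteria, so early extubation or decannulation should not arise. This weakens the argument for patients coming off support. It does not settle it, because Section 2.6 and Table 6 place screening and allocation at ECMO initiation, when ECMO duration cannot yet be known. Deaths in the window are in any case provided for in Table 6.

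A third reply is that worst-case bounds can be drawn for any trial with 5% missing data. That is fair, and the size of the point has to be stated conditionally. The imputation method may also belong in an analysis plan that is not shown; its absence is not part of this point.

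**Conclusion.** The point holds as an inconsistency to be resolved: Sections 2.5, 2.7, 2.8, 2.9.2 and 2.9.3 and Table 6 need to be reconciled. As written, the primary result could rest on completers, and the T1–T3 comparisons could be of survivors only.

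A reader might go further and infer that the missing 5% could reverse a positive finding. The figures do not support that. Even at the extreme of 0 against 28, the difference at the design effect stays positive (0.63 VFD); what is lost is significance. Balanced dropouts with similar outcomes leave p at 0.005 to 0.006. Loss of significance at 2.1 VFD needs 0 against about 11.8 or more, or nearly all dropouts in the intervention arm with 0 VFD. The result becomes fragile only if the observed effect is about 1.5 to 1.8 VFD.

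These figures rest on the design means and SDs, a t-test, 15 missing per arm (except for the uneven splits), a VFD range of 0 to 28, and 9.2 being the intervention mean. The T1–T3 part is a matter of logic, and its size cannot be given from the article.

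**What to change.** Replace the sentence in Section 2.7 with three rules:

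1. Patients who stop the assigned strategy or withdraw are followed through hospital records to day 28, unless consent for data use is withdrawn. Day-28 contact stays for those discharged alive.
2. All randomised patients enter the primary analysis in their allocated arm. Any missing VFD is imputed, and a tipping-point sensitivity analysis varies the imputed values separately by arm.
3. T1–T3 measures are analysed with the T0 value as covariate, for example in a repeated-measures model. The numbers dead or off support are reported by arm at each time, and the estimates are read as conditional on being alive.

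The wording should add that in-hospital missingness is expected to be rare, if that is what is meant, and that the 5% in Section 2.8 is a sample size allowance and not an exclusion from analysis. The cost is a change of wording and a little more analysis work. The records are already the data source and the T0 values are already collected.

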### Sample size calculation

2.8.

PASS 11 was used for sample size calculation, where a sample size of 292 patients per group would achieve 80% power to detect a difference between the two groups, providing the means were 7.1 and 9.2 with group standard deviations of 8.8 and 9.3 and with a significance level α of 0.05 using a two-sided two-sample *t*-test. Accounting for an anticipated dropout rate of 5%, 614 patients were required for the study.

### Statistical methods

2.9.

#### Descriptive analysis

2.9.1.

We will describe the demographic and clinical characteristics and compare them between the groups. All data will be given in the form of mean ± standard deviation values or medians with interquartile ranges specific to continuous variables or in the form of percentages specific to categorical variables. Student's *t* test and the Mann–Whitney *U* test will be used for comparing quantitative characteristics specific to normally and non-normally distributed variables, respectively. The *χ*^2^ test or Fisher's exact test will be used for comparing qualitative characteristics.

#### Primary outcome analysis

2.9.2.

The primary outcome is the 28-day VFD number, which will be determined by the intention-to-treat analysis (ITT) (21), regardless of whether the allocated ventilation strategy was effectively applied or not. The primary outcome will be reported in each group in the form of means with standard deviation values or medians with interquartile ranges. Student's *t* test or the Mann–Whitney *U* test will support related comparisons of the 2 groups while considering their distribution characteristics.

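### The primary test is left to the observed distribution, but the 80% power is established only for the t test on mean VFDs, and the planned figures point towards Mann–Whitney

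*Protocol article*

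**What the plan says.** Section 2.9.2 states "The primary outcome is the 28-day VFD number", analysed by intention to treat. It allows either means with SDs or medians with interquartile ranges as the summary. For the comparison, Student's t or the Mann–Whitney U "test will support related comparisons of the 2 groups while considering their distribution characteristics". No criterion for choosing is given there.

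The explicit mapping stands one section earlier, in 2.9.1 (Descriptive analysis): Student's t and the Mann–Whitney U "test will be used for comparing quantitative characteristics specific to normally and non-normally distributed variables, respectively".

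Section 2.8 has only one test in view: "a sample size of 292 patients per group would achieve 80% power", "providing the means were 7.1 and 9.2 with group standard deviations of 8.8 and 9.3", "with a significance level α of 0.05 using a two-sided two-sample" t test.

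**The concern.** The two tests answer different questions. The t test compares mean VFDs. Mann–Whitney compares the chance that a patient in one arm has more VFDs than a patient in the other. For a normal outcome the choice hardly matters, but VFDs are bounded and typically pile up at zero, and there the two can differ widely in power.

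The sample size is tied to the t test, while the analysis section leaves open a switch away from it. If the switch is made, the trial's main result comes from a test whose power was never worked out, and the effect reported (medians) is not the 2.1-day difference in means that the trial was sized to find.

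**Working it through.** **Inputs.** From section 2.8: means 7.1 and 9.2, SDs 8.8 and 9.3, two-sided α 0.05, 292 per arm. The zero share is not in the document and is varied as an assumption.

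**1. Reproduce the plan's figure.** n per arm = (1.960 + 0.842)² × (8.8² + 9.3²) / (9.2 − 7.1)² = 7.849 × 163.93 / 4.41 = 291.8, so 292. Power at 292 is 80.0% by the normal formula and 79.9% by the noncentral t. The stated figure is right for the t test.

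**2. Can the outcome be normal?** VFDs cannot be below 0. Normal curves with the planned values would put Φ(−7.1/8.8) = Φ(−0.807) = 21% of control patients and Φ(−9.2/9.3) = Φ(−0.989) = 16% of intervention patients below zero. So the outcome is not normal on the plan's own figures, and the 2.9.1 convention would select Mann–Whitney.

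**3. Power of both tests at 292 per arm.** Model: a point mass at zero plus a discretised beta distribution on days 1–28, fitted in each arm to the planned mean and SD. There were 20,000 simulated trials per row (4,000 for the last), with a tie-corrected Mann–Whitney.

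| Zero share, control / intervention | t test | Mann–Whitney |
|---|---|---|
| 45% / 45% | 80% | 48% |
| 40% / 40% | 80% | 52% |
| 30% / 30% | 80% | 64% |
| 50% / 45% | 80% | 65% |
| 55% / 45% | 80% | 78% |
| 50% / 40% | 80% | 79% |
| 45% / 35% | 80% | 82% |
| 50% / 35% | 79% | 90% |

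Shorter repeat runs gave 46–48% for 45/45 and 60–64% for 30/30; the t test stayed at 78–81%. With truly normal data Mann–Whitney would have about 78%, so the loss comes from the shape of VFDs, not from the rank test as such.

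**4. What the equal-zero rows require.** With zero share p, the mean among non-zero patients is mean/(1 − p), and the variance is (SD² + mean²)/(1 − p) minus the square of that mean.

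- 45/45: control 7.1/0.55 = 12.9, SD √(127.85/0.55 − 12.91²) = 8.1; intervention 9.2/0.55 = 16.7, SD √(171.13/0.55 − 16.73²) = 5.6.
- 30/30: 10.1 (SD 8.9) against 13.1 (SD 8.5).
- 50/40: 14.2 (SD 7.4) against 15.3 (SD 7.1).

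The lowest power therefore needs a gain of almost 4 days among non-zero patients together with a marked narrowing of their spread. The 30/30 row needs no such narrowing and still gives about 64%.

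**The case against.** The strongest reply has four parts.

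- **A reader might infer that power falls to about 47%.** The documents do not support that as a headline. It needs a high zero share, equal in both arms, which the protocol does not give, and the narrowing shown above. The Introduction hopes for lower mortality as well as easier weaning, and mortality is the first secondary objective. If death is scored as zero VFDs, lower mortality means fewer zeros in the intervention arm, and there Mann–Whitney loses little or gains. This stands, so only a range can be reported. The range is itself model-dependent. If VFDs could not exceed 25 (28 minus the 72-hour intervention), the equal-zero cases at 45–47% fall to about 39–41%, while the 10-point cases stay at 78–81%.
- **A reader might infer that section 2.9.2 mandates Mann–Whitney.** It does not. The normal/non-normal mapping is written for descriptive characteristics, and 2.9.2 refers only to distribution. A t test remains open under its wording. This stands, but it leaves the mismatch: one of the two permitted tests has no power basis.
- **A reader might infer that the choice inflates the type I error.** That would follow from picking whichever test is significant. The written rule selects on distribution, and section 2.5 keeps analysts and statisticians unaware of allocation. This claim is not made.
- **Such detail may belong in an analysis plan that is not shown.** That would answer a silence. Here the protocol itself states an either/or rule that does not fit its own sample-size basis.

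**Conclusion.** The point holds in this form: the primary test and summary are left to the observed distribution, while 292 per arm and 80% power are established only for the t test on means. The planned means and SDs rule out normality, so the article's own convention, carried over to the primary outcome, would lead to the test that was not powered.

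The size of the loss is uncertain. Mann–Whitney power is about 46–64% if the zero share is equal in both arms (45% down to 30%) and the gain lies in non-zero VFDs. It is about 65% with 5 points fewer zeros in the intervention arm, and about 79–90% with 10–15 points fewer. These figures rest on assumed zero shares and on the zero-plus-beta model. The mismatch itself rests on neither.

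**What to change.** Name one primary test and one effect measure in section 2.9.2, to apply whatever the observed shape.

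- **Cheapest, and consistent with section 2.8:** the difference in mean VFDs with a 95% CI, by Welch t test or a linear model with robust standard errors. Mann–Whitney becomes supportive, and mortality and ventilator days in survivors are reported beside it. No change in sample size is needed. The drawback is that a mean difference is less intuitive for an outcome with many zeros, which reporting the components covers.
- **If a rank test is preferred as primary:** restate the power for that test under stated zero shares. In the model above, 80% power would need about 426 per arm at 30/30, 628 at 45/45 and 295 at 50/40.

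Table 2 records that enrolment has not begun, so the first option is a wording change that can be made before any outcome data exist.

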#### Secondary outcomes analysis

2.9.3.

The intention-to-treat analysis will help in assessing the results of the secondary outcomes. Qualitative secondary outcomes, such as the in-hospital mortality rate in each group, will be reported, and the *χ*^2^ test or Fisher's exact test will be used for the comparison. Quantitative secondary outcomes, such as LUS, will be described in each group in the form of medians with standard deviation values or medians with interquartile ranges, considering the distribution shape, and Student's *t* test or the Mann–Whitney *U* test will support related comparisons between the 2 groups. Stata version 16 (StataCorp LLC, College Station, TX, USA) will assist in carrying out all analyses. A bilateral *p*-value of <0.5 will be used to indicate statistical significance.

Performing an interim analysis will be mandatory in order to check whether there are any inappropriate operations related to data collection or management.

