1.To examine whether ultra-protective VT can decrease the all-cause in-hospital mortality rate2.To examine whether ultra-protective VT can reduce the time for successful VA-ECMO weaning (Table 4)3.To examine whether ultra-protective VT is associated with a shorter ICU length of stay4.To examine whether ultra-protective VT is associated with a reduction in interleukin-6 (IL-6), interleukin-8 (IL-8), and monocyte chemotactic protein-1 (MCP-1) levels in broncho-alveolar lavage fluid (BALF)5.To examine whether ultra-protective VT affects respiratory parameters (e.g., total PEEP, plateau pressure [P_plat_], driving pressure [DP], airway resistance [R], static compliance [C_stat_], mean airway pressure [P_mean_], esophageal pressure [P_es_], transpulmonary pressure [P_tp_], and mechanical power [MP]), based on a daily assessment from inclusion to closeout (14)6.To examine whether the ultra-protective VT strategy decreases the lung ultrasound score (LUS) (Figure 1 and Table 5) when assessed daily from inclusion to closeout (15, 16)7.To examine whether ultra-protective VT can lead to an increased analgesic/sedation dosage during the intervention period after inclusion8.To examine whether ultra-protective VT predicts a decrease in the total hospitalization cost9.To examine whether ultra-protective VT is associated with a reduced demand for fluid resuscitation

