### Interventions

2.6.

At the onset of ECMO initiation, all participants will be screened by therapists. Once the patient meets the inclusion criteria and is finally enrolled, the therapists will provide the selected intervention. We will assign patients in the intervention group to receive ultra-protective VT after randomization (initial settings: VT, 4 ml/kg of PBW; PEEP, 10 cmH_2_O; respiratory rate, 10 min^−1^; Vt may be decreased stepwise by 0.5 ml/kg PBW if the plateau pressure is >30 cmH_2_O) (17).

Patients in the control group will be managed using a protective VT strategy after randomization (initial settings: VT, 6 ml/kg of PBW; PEEP, 10 cmH_2_O; respiratory rate, 10 min^−1^; Vt may be decreased stepwise by 0.5 ml/kg of PBW if the plateau pressure is >30 cmH_2_O).

We will set the sweeping gas flow of ECMO, targeting a PaCO_2_ range of 35–45 mmHg, and the FiO_2_ value of the ventilator may be increased if PaO_2_ in the right upper limb decreases to <60 mmHg during the course of Vt and PEEP adjustments.

Furthermore, a hybrid veno-arterio-venous ECMO mode will be considered if differential oxygenation happens (18). Differential oxygenation refers to the lower body being perfused by ECMO-oxygenated blood while the upper body (coronaries, right arm, brain) receives hypoxemic blood pumped by the native heart. This pathophysiological phenomenon often results from the recovery of native left ventricular function and simultaneous severe lung failure. If optimized ventilation fails to solve this issue, it will be necessary to employ veno-arterio-venous ECMO in consideration of the potential for hypoxic damage to the brain and heart (19, 20).

At the moment of enrollment (T0), investigators will take charge of assessing and collecting pre-defined respiratory mechanics parameters; IL-6, IL-8, and MCP-1 levels; LUS; and other trial data as baseline information. The same procedure will be performed repeatedly at 24, 48, and 72 h (T1, T2, and T3, respectively) after ECMO initiation (Figure 2). After 72 h, the mechanical ventilation strategy in both groups will be changed at the intensivists' discretion.

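### LUS, BALF cytokines and respiratory mechanics have a T0 value and three follow-ups, but the stated two-group test has no T0 covariate and does not model the repeats; the objectives' window for mechanics and LUS also contradicts the schedule

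*Protocol article*

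**What the plan says.** **Measurement.** Section 2.6 (Interventions) has investigators collect respiratory mechanics, IL-6, IL-8, MCP-1, "LUS; and other trial data as baseline information" at enrolment (T0). It continues: "The same procedure will be performed repeatedly at 24, 48, and 72 h (T1, T2, and T3, respectively) after ECMO initiation". The abstract gives the same four times, and Table 6 marks the mechanics, LUS and BALF rows at T0, T1, T2 and T3 only.

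**Analysis.** Section 2.9.3 (Secondary outcomes analysis) takes LUS as its example of a quantitative secondary outcome: "Quantitative secondary outcomes, such as LUS, will be described in each group". It then says "Student's *t* test or the Mann–Whitney *U* test will support related comparisons between the 2 groups", with the choice depending on the shape of the distribution. It names no covariate, change score, repeated-measures model or analysis time point.

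**Window.** In section 2.2 (Trial objectives), objective 5 (mechanics) is "based on a daily assessment from inclusion to closeout" and objective 6 (LUS) applies "when assessed daily from inclusion to closeout". Objective 4 (cytokines) states no such window. Table 6 places close-out at day 28 and at ICU discharge, and neither mechanics nor LUS is marked there.

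**The concern.** Two separate matters arise.

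First, the design pays for a baseline and three follow-ups of each of these outcomes, including repeated bronchoalveolar lavage, but the stated test is built for one value per patient. Patients' T0 values will differ widely for reasons unrelated to treatment, and simple randomisation (section 2.5) does nothing to balance them. A comparison without T0 carries that variation in its standard error. With no contrast named, it is also unclear which of the three follow-ups the test concerns.

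Second, the objectives and the schedule describe different data sets for mechanics and LUS. After 72 h ventilation is left to the treating intensivists (section 2.6), so later mechanics no longer reflect the allocated strategy. Plateau pressure, driving pressure and mechanical power on the ventilator exist only in patients still alive and ventilated. Who those patients are may depend on treatment, since time off the ventilator is the primary outcome. If both windows stay in the plan, the choice between them could be made after the data are seen.

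**Working it through.** **1. The plan's own sample size.** Inputs from section 2.8: means 7.1 and 9.2, SDs 8.8 and 9.3, two-sided α 0.05, power 80%.

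- Pooled SD = √[(8.8² + 9.3²)/2] = √81.965 = 9.053; difference = 2.1, or 2.1/9.053 = 0.232 SD.
- n per group = 2 × (1.960 + 0.842)² × 81.965 / 2.1² ≈ 291.8, so 292, as stated.
- 292 × 1.05 = 306.6, so 307 per group and 614 in total, as stated.

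This figure concerns ventilator-free days and does not depend on the present point. The protocol states no power for LUS, cytokines or mechanics. I use 292 per group below only to put the precision loss on a scale.

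**2. Gain from adjusting for T0.** For one follow-up time, with ρ the correlation between the T0 and follow-up values, the residual variance is multiplied by 1 − ρ². The difference detectable with 80% power, in SD units, is (1.960 + 0.842) × √(2/292) × √(1 − ρ²) = 0.232 × √(1 − ρ²). The last column gives the power for a true effect of 0.232 SD.

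| ρ (assumed) | Variance remaining | Variance removed | Detectable difference (SD) | Power |
|---|---|---|---|---|
| 0 (unadjusted) | 1.00 | 0% | 0.232 | 80% |
| 0.3 | 0.91 | 9% | 0.221 | 84% |
| 0.5 | 0.75 | 25% | 0.201 | 90% |
| 0.7 | 0.51 | 49% | 0.166 | 97.5% |

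**3. Validity of the unadjusted test.** In 4,000 simulated trials with no effect for each of ρ = 0.3, 0.5 and 0.7 (292 per group, test at 5%), the unadjusted t test rejected in 4.7% to 5.4% and the T0-adjusted analysis in 4.8% to 5.1%. Both hold the nominal level.

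**4. If the test were applied to change from T0.** With equal variances at T0 and follow-up, the variance factor is 2(1 − ρ): 1.4, 1.0 and 0.6 at ρ = 0.3, 0.5 and 0.7. The covariate approach gives 0.91, 0.75 and 0.51, which is smaller each time. At ρ = 0.3 a change score is less precise than ignoring T0.

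**5. The window, side by side.**

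| Outcome | Objectives (2.2) | Section 2.6 and Table 6 | Conflict |
|---|---|---|---|
| Respiratory mechanics | Daily to closeout | T0, 24, 48, 72 h | Yes |
| LUS | Daily to closeout | T0, 24, 48, 72 h | Yes |
| BALF cytokines | No window stated | T0, 24, 48, 72 h | No |

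Close-out in Table 6 is day 28 or ICU discharge, so it cannot be read as 72 h to make the two agree.

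**The case against.** The strongest reply is that nothing here is an error of inference. Under 1:1 randomisation the unadjusted test is valid, its standard error already allows for chance imbalance, and step 3 confirms this. That stands in full.

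A second reply is that section 2.9.3 names a family of tests, not the variable tested. A t test on change from T0 would fit the wording, and an analysis plan not shown here may name the time point or a fuller model. This stands in part. The missing detail is not itself a fault, and the protocol does not say that it will test each time point separately. But the article does state a method for these outcomes, and even on the change-score reading the covariate model is more precise (step 4).

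A third reply is that the size of the gain has no source in the protocol. That is right: it is conditional on ρ.

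A reader might also infer more than the text supports:

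- *That every comparison ignores baseline.* Ventilator-free days, mortality, ICU stay, time to ECMO weaning, cost, and sedation and fluid amounts have no T0 value of the outcome to adjust for.
- *That the primary analysis is wrong.* Section 2.9.2 says "Student's *t* test or the Mann–Whitney *U* test will support related comparisons of the 2 groups", and its t test option matches the sample-size method. Adjusting for age and APACHE II, both listed in section 2.7, is an optional efficiency gain. Any figure for patients saved would only restate an assumed share of explained variance. Arrest versus shock is not listed as a data item.
- *That all late data come from ventilated survivors.* That holds for ventilator mechanics. Nothing in the definition of LUS requires ventilation.

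**Conclusion.** The point holds for LUS, BALF cytokines and respiratory mechanics only. The stated test is valid but inefficient: 9%, 25% or 49% of residual variance could be removed at an assumed ρ of 0.3, 0.5 or 0.7. These figures apply to one follow-up time, assume a linear relation with T0, and require T0 to be measured before the allocated setting takes effect. The true gain may differ by outcome. This is an available improvement, not a defect that would invalidate the trial.

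The window conflict for mechanics and LUS is certain and needs no assumption. It touches two secondary objectives. It does not extend to cytokines, and the sample size of 614 is unaffected by either matter.

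**What to change.** 1. In section 2.9.3, for LUS, IL-6, IL-8, MCP-1 and respiratory mechanics only, replace the two-group test with one repeated-measures model per outcome. The responses are the T1, T2 and T3 values. The terms are treatment, time, treatment-by-time and the T0 value as covariate, with within-patient correlation modelled and cytokines on the log scale. Name in advance one contrast per outcome, for example the treatment difference at T3 or averaged over T1 to T3.
2. Reconcile objectives 5 and 6 with the abstract, section 2.6 and Table 6, so that one schedule is stated throughout. Whichever schedule is kept, base the between-group comparison on T1 to T3 and treat any later values as descriptive.
3. Optionally, adjust the primary comparison for age and APACHE II, if this is fixed before unblinded data are seen.

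The cost is some extra programming and a wording correction. Items 1 and 3 use data already planned. Item 2 needs new assessments only if the sponsor chooses to keep the daily window and extend Table 6 to match.
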